g. BASDAI, ASDAS, PASS, PhASS, patient and physician global assessment only.

h. 12-lead electrocardiography (ECG).

i. Lab tests to be performed locally at the clinical trial site: Blood chemistry (total bilirubin, ALT, AST, GGT, AP, creatinine), hematology (erythrocytes, hemoglobin, leucocytes, neutrophils, lymphocytes, monocytes, basophils, eosinophils, platelets), CRP and ESR.

j. Lab test at screening should include also Quick-Test, International Normalized Ratio (INR) and activated Partial Thromboplastin Time (aPTT)

k. Biomarker blood samples (soluble and cellular markers of inflammation, cartilage and bone turnover) to be transferred to the Charité Universitätsmedizin Berlin.

l. Female patients of child-bearing potential only.

m. Stool samples for the microbiome analysis to be transferred to the Charité Universitätsmedizin Berlin.

n. Chest x-ray & tuberculosis serum IGRA test (QuantiFERON® TB Test or T SPOT.TB®) performed within 3 months prior to screening can be accepted.

o. X-rays of the lumbar and cervical spine, lateral views; to be performed at screening only if there is no image performed within 24 months prior to screening; at visit "Week 108/ET" – to be performed only at or after week 84 in case of early termination. All images of the spine to be transferred to the study coordinating centre at the Charité for central reading.p. For centres and patients participating in the MRI sub-study only. At visit "Week 108/ET" only to be performed at or after week 84 in case of early termination.

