6 INVESTIGATIONAL PLAN

6.1 Study Design

The study duration includes two phases (Figure 1):

[figure not shown]

- **Phase I (Run-in Phase):** It includes a screening period of ≤6 weeks followed by a 12-week period where all patients receive treatment with Golimumab 50 mg SC every 4 weeks.

**Screening:** Patients will be assessed for study eligibility and will undergo procedures outlined in the visit schedule. During this period a standard chemoprophylaxis of tuberculosis might be initiated if appropriate prior to the first injection of Golimumab. Subjects, who were initially regarded as screen-failures for the study, may be permitted to rescreen once following signing re-consent and require a repeat of the screening procedures.

Baseline: eligibility assessment and start of Golimumab 50 mg SC treatment.

Visits Week 2, 4 and 8: safety assessment according to the recommendations for anti-TNF treatment.

- **Phase II (Core Phase):** it is composed by a 96-week controlled treatment period and a safety follow-up visit at week 112.

Visit at Week 12: assessment of clinical response (achievement of at least 2 absolute points on a scale from 0-10) after 12 weeks of TNF-Blocker treatment in the phase I. Only patients who achieve a good clinical response will be included and randomized 1:1 to receive Golimumab 50mg SC every 4 weeks alone or in combination with Celecoxib 400mg per os daily.

Visits Week 24, 36, 48, 60, 72, 84, and 96: safety assessment according to the current recommendations for anti-TNF therapy (every 3 months); clinical disease activity assessment.

Visit at Week 108 or Early Termination: After the last Golimumab injection at Week 104 or in case of early termination (ET, only in patients who were randomised for further therapy at week 12 of the study).assessment of the primary (radiographic progression) and secondary end-points including safety assessment. A second set of X-rays of the spine and a second MRI of spine and sacroiliac joints (for patients participating in the MRI sub-study) are only to be taken, if the patient reached at least the Week 84 time point. There will be a follow-up period of 4 weeks with a safety follow-up visit (phone call) for the collection of additional safety information.

Visit at Week 112 / Follow-up (FU):

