## 6.6 Study Discontinuation

### 6.6.1 Discontinuation of Individual Subjects

A subject may withdraw from the study at any time. The investigator may discontinue the subject participation due to adverse events, safety concerns or subject's failure to comply with the protocol.

Subjects will be withdrawn from the study if one of the following occurs:

- The subject requests withdrawal from the study.
- The subject does not achieve a good clinical response (improvement of at least  $\geq 2$  absolute points on a 0-10 scale of BASDAI after 12 weeks of treatment with Golimumab in the phase I.
- The female subject of child-bearing potential does not perform effective contraceptive methods or becomes pregnant during the study.
- The subject is diagnosed with a malignancy or lymphoproliferative disorder.
- The subject develops allergic reaction to / intolerance of the study drug.
- The subject is diagnosed with multiple sclerosis or demyelinating disease.
- The subject develops a lupus like syndrome.
- Two consecutive Golimumab injections were not performed.
- For patients in the combination arm: Study treatment with Celecoxib was interrupted for more than 4 weeks.
- Introduction of a prohibited medication after the subject started the study drug, when continuation of the study therapy would place the subject at risk as defined by the investigator.
- The subject receives a live vaccine during the study period.
- Major surgical intervention during the study period.
- The subject is diagnosed with active tuberculosis, opportunistic infection or any other severe infection including acute Hepatitis B or HIV.
- Subject is non-compliant with anti-tuberculous treatment (if this medication is required).

- Any AEs, including clinically significant laboratory abnormalities, when continuation of the study therapy would place the subject at risk as defined by the investigator.
- Any other reason at the investigators discretion to ensure the well-being of the subject.

In case of premature discontinuation of the study procedures outlined in the assessment schedule for the “Early Termination Visit” should be performed within 4 weeks after last dose of study drug. The reason for the discontinuation must be documented. After study discontinuation the patients will be treated according to available standards of care.

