### 13.8 Sample Size and Power Calculation

The study is designed for a total sample size of  $n = 170$  subjects who will enrol in the phase I of the study. The power calculations are based on the findings of Kroon et al, our own results from GESPIC Cohort, and those of Braun et al. We assume a worsening in the mSASSS score of  $1.7 \pm 2.8$  in patients of the control group and of  $0.2 \pm 1.6$  in patients with continuous NSAIDs intake. We considered such a difference of 1.5 mSASSS units as clinically relevant and planned the sample size of this study by means of a two-sided ( $\alpha = 0.05$ ) Welch-Satterthwaite t-test accordingly. A smaller treatment effect, which was

observed in a trial comparing diclofenac continuously vs. on demand and which would be missed by our trial design, would be considered as clinically not relevant. To detect the difference with an 80% power, the sample size of  $n = 38$  in each group is needed in the phase II of the trial. This is also true if the Mann-Whitney test is applied. Since in the case of skewed non-normal distributions (like the mSASSS) the power of the Mann-Whitney-test is not lower than that of the t-test even in the case of ties (Rasch D et al, 2007). However, the power will decrease by the application of multiple imputations to deal with missing radiographs of dropouts in the ITT population. We estimated this decrease by: a) an estimation of dropout rates and b) the use of own mSASSS data. Considering that all subjects enrolled in the phase II will be responders to Golimumab therapy receiving this same treatment for the whole period of the trial, along with our experience in conducting randomized controlled trials, we presume dropout rates of less than 20% during phase II. For this reason and based on our own mSASSS data, we expect an increase in the variance of mSASSS progression because of multiple imputation by less than 25%. Considering this possible increase, a sample size of  $n = 100$  patients is needed for phase II of the trial to detect the expected and clinically relevant difference of an average 1.5 mSASSS points with an 80% power in the ITT population. In addition we assumed that 60% of the subjects enrolled in phase I of the study ( $n = 100$  out of 170) would be eligible for randomization and participation in phase II (based on the rate of the BASDAI response of at least 2 absolute points in AS patients with elevated CRP).

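### Stopping study treatment means leaving the study, and no second spinal film is taken before week 84, so some randomised patients lose the primary outcome by rule, with one withdrawal trigger that exists only in the combination arm

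*Protocol*

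**What the plan says.** Protocol section 6.6.1 has a single list, introduced by "Subjects will be withdrawn from the study if one of the following occurs". It mixes withdrawal at the patient's own request with treatment events: intolerance of study drug, two consecutive missed golimumab injections, a live vaccine, major surgery, and adverse events that make further therapy risky. One entry is specific to an arm: "For patients in the combination arm: Study treatment with Celecoxib was interrupted for more than 4 weeks". No status is described in which a patient is off treatment but still followed for outcome. A withdrawn patient has an early-termination visit within 4 weeks of the last dose and then goes to standard care, with a telephone safety follow-up.

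Spinal films are scheduled twice, at screening (or an existing film up to 24 months old) and at week 108 or early termination. Section 6.1 says that the second films "are only to be taken, if the patient reached at least the Week 84 time point". For early termination, footnote o of the assessment schedule (section 3) says "to be performed only at or after week 84 in case of early termination", and section 6.7 gives the same rule.

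Section 13.5 bases the primary analysis on everyone who entered phase II. It fills in missing films by multiple imputation, with baseline mSASSS as the only covariate named. Section 13.2 defines the ITT population more narrowly: the primary variable must have been measured at least once while on study medication. Section 13.7 lists the handling of missing films in the analysis as one of its three safeguards against bias.

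**The concern.** The primary endpoint is the change in mSASSS between two films. A patient withdrawn after randomisation but before week 84 never has the second film, although one could still be taken at week 108. The loss follows from the rules and is tied to treatment events. One trigger can act in only one arm. A control patient who starts on-demand NSAIDs within the permitted limit stays in the study and is filmed. A combination patient who is off celecoxib for more than 4 weeks must leave, and before week 84 leaves without a film.

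This is a problem of data collection that a later analysis plan cannot repair. No patient withdrawn before week 84 contributes an off-treatment film, so any imputation for them borrows from patients whose films were obtained under the protocol. At stake is whether the as-randomised comparison promised in 13.5 can be made, and whether the groups with observed films are still comparable. Read literally, section 13.2 would go further and drop these patients from the ITT population altogether, which contradicts 13.5.

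**Working it through.** **Inputs.** From section 13.8: control change 1.7 (SD 2.8), combination change 0.2 (SD 1.6), difference 1.5, two-sided alpha 0.05, power 80%, dropout below 20% in phase II with no split by arm, and a variance increase from imputation below 25%. From 6.1: the randomised period runs from week 12 to week 108 (96 weeks). From section 2: 50 patients per arm.

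**1. The plan's own figure.** Welch test with SE = sqrt((2.8² + 1.6²)/n) and noncentrality 1.5/SE. At n = 38, SE = sqrt(10.4/38) = 0.523 and power is 80.5%; at n = 37 it is 79.4%. So 38 per group reproduces. With variance multiplied by 1.25, 47 per group are needed (80.4%), and the planned 50 give 82.8%. The sample size is not in error, but it treats missing films only as a cost in variance and allows nothing for bias or unequal loss.

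**2. Films lost by rule.** Weeks 12 to 84 are 72 of 96 weeks, or 75%. At the 20% ceiling, with dropout spread evenly, 0.75 × 20 = 15 of 100 patients have no second film. If all dropout came before week 84, it would be 20. Both figures count every dropout. Patients who withdraw consent or are lost to follow-up would have no film under any rule, so fewer than these are recoverable.

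**3. Illustrative effect on the comparison.** Assumption, not in the document: 20% of the combination arm stops celecoxib before week 84 and then progresses at the control rate, while all other patients behave as planned.

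- As-randomised difference, stopping at the start: 1.5 × (1 − 0.2) = 1.20.
- As-randomised difference, stopping half-way: 1.5 × (1 − 0.2 × 0.5) = 1.35.
- Complete-radiograph analysis, or imputation within arm: still aims at 1.7 − 0.2 = 1.5.
- Arm-free imputation, loss in the combination arm only: pooled mean of observed patients (50 × 1.7 + 40 × 0.2)/90 = 1.03; combination mean 0.8 × 0.2 + 0.2 × 1.03 = 0.37; difference 1.7 − 0.37 = 1.33.
- Arm-free imputation, 20% lost in both arms: pooled mean 0.95; control 0.8 × 1.7 + 0.2 × 0.95 = 1.55; combination 0.8 × 0.2 + 0.2 × 0.95 = 0.35; difference 1.20.

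The arm-free calculation ignores baseline mSASSS, which amounts to assuming that it is balanced and does not separate the lost patients from the others.

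**4. Power if every film were obtained, 50 per arm, Welch approximation.** About 68% at a difference of 1.20 (stoppers given the control mean and SD) and about 83% at 1.35 (stoppers given a mean of 0.95 and SD 1.6).

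**5. The two ITT statements.** A patient withdrawn at week 40 has entered phase II and belongs to the 13.5 population. The same patient has no mSASSS measured on study medication in phase II and is outside the 13.2 population on a literal reading. If 13.2 governs, there is nobody of this kind left to impute.

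**The case against.** The strongest reply concerns direction and size. A reader might infer that the plan overstates the effect of celecoxib by 11% to 25% (1.5/1.35 and 1.5/1.20), in favour of the combination. The document does not support that for the primary analysis. Section 13.5 does not say whether imputation is done by arm. As step 3 shows, arm-free imputation gives 1.33 or 1.20, inside the illustrative as-randomised range. No celecoxib-stopping rate is documented, and the 20% ceiling is for overall dropout. The 11% to 25% fits only the complete-radiograph analysis or imputation within arm, under the assumed stopping rate. This part of the reply stands.

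A reader might also infer that celecoxib-tolerant patients are compared with nearly all controls. That is not supported either: most triggers in 6.6.1 apply to both arms, and no rate by arm is given. The protocol also limits celecoxib losses. It permits interruptions of up to 4 weeks and a dose reduction, and it excludes patients with known intolerance of celecoxib or previous severe reactions to NSAIDs.

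Finally, the endpoint is worded as change over two years of therapy, and a film taken after treatment has stopped or changed answers a different question. That is a fair account of what the fix costs. It does not remove the point, because 13.5 states an analysis of all who entered phase II, and that analysis needs outcomes from them. The week-84 floor is sensible for a film taken at early termination, where the interval would otherwise be short. It is no reason to forgo a film at the scheduled week 108.

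**Conclusion.** The concern holds as a matter of data collection. Patients withdrawn between weeks 12 and 84 have no post-baseline mSASSS by rule, one withdrawal trigger acts only in the combination arm, and imputation on baseline mSASSS has no off-treatment data to draw on. The ITT definition in 13.2 contradicts the population in 13.5.

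Up to about 15 of 100 patients are affected at the 20% ceiling with even dropout, and fewer are recoverable. Neither the size nor the direction of bias can be fixed from the document. The 1.20 to 1.35 as-randomised range rests on an assumed 20% celecoxib-stopping rate and on progression at the control rate afterwards. It shows what could be hidden and is not a forecast. The change is a cheap improvement to the as-randomised comparison and does not show that the planned result would be biased towards the combination.

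**What to change.** - In 6.6.1, separate discontinuation of study treatment from withdrawal from the study. Leave the treatment-stopping criteria as they are.
- Keep patients who stop treatment in follow-up and take the already planned spinal film at the scheduled week 108, unless consent is withdrawn or imaging is not appropriate (pregnancy, for example).
- Keep the week-84 floor for any film taken at an early-termination visit, so that no short-interval films are introduced. Align section 3, 6.1 and 6.7 with this.
- Use the week-108 films in the as-randomised primary analysis, with imputation left for films that cannot be obtained.
- Reconcile 13.2 with 13.5 so that all randomised patients are included.

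The cost is an amendment with consent wording, and a follow-up visit and film for up to about 15 patients under the even-dropout assumption. Some films will be taken after treatment was stopped or changed, so the estimate is as-randomised rather than on-treatment. If many patients stop celecoxib, that difference, and the power to detect it, will be smaller than planned.

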## 6.2 Justification of Design aspects

### 6.2.1 Control(s) / Comparator(s)

The core phase of the study compares the effect of TNF-blocker alone vs. adding an NSAID to the anti-TNF therapy on the radiographic progression in patients with active AS. For NSAIDs, Celecoxib was chosen as preferred NSAID among the others because up to date

Celecoxib is the only NSAID that has shown an inhibitory effect on radiographic spinal progression in AS. Furthermore, there has been some evidence that Celecoxib might have a specific effect on osteoblast metabolism, not shared by the other NSAIDs. These data justified, therefore, the choice of Celecoxib as a study drug.

For the TNF-blockers, we do not expect any differences regarding their inhibitory effect on radiographic spinal progression. Golimumab was selected based on the availability; in general, a similar efficacy of all anti-TNF-blockers can be assumed.

In the Golimumab-combined-Group, patients will be treated with a full therapeutic dose (400 mg/d) of Celecoxib and Golimumab 50 mg every 4 weeks. For the control group – Golimumab-Monotherapy-Group (they will receive Golimumab 50 mg every four week alone), patients and physicians will be encouraged to discontinue NSAIDs at week 12 and treat patients with analgesics (not NSAIDs) if necessary. However, in order to increase acceptance of this study, adding NSAIDs intake on demand as a rescue medication will be allowed in the control group if demanded by patient or physician (as it was performed on the control group of the study cited above). In the case of rescue therapy with an NSAID in the monotherapy group not more than 50% of the maximal recommended dose will be permitted, but under no circumstance Celecoxib should be taken in the control group.

### 6.2.2 Dose, Mode, Duration and Scheme of Intervention

In the phase I of the study, patients with clinical indications for anti-TNF therapy (high disease activity despite treatment with NSAIDs – first line therapy) will be treated for 12 weeks with an approved dose of the TNF-blocker Golimumab 50mg SC every 4 weeks. During this period, patients shall take their NSAID in a stable dose during the first 12 weeks of the study. Any change in the dose or of the intake regimen is allowed only for a safety reason as judged by the investigator. After 12 weeks of treatment, good clinical responders will be randomized to receive treatment with Golimumab (50 mg SC every 4 weeks) and Celecoxib in full therapeutic dose (400 mg per os daily) or Golimumab (50 mg SC every 4 weeks) alone for another 96 weeks in order to assess the course of radiographic progression of the spine.

Currently, 2 years is the standard minimal duration of the study aimed at the assessment of radiographic spinal progression in ankylosing spondylitis.

In the combined treatment group, a Celecoxib interruption of max. 4 weeks duration will be allowed if medically justified (i.e., intolerability / side effects associated with the full NSAID

dose); a dose reduction to 200 mg/d is possible for better acceptance or safety issues (due to the discretion of the investigator), the reason for dose reduction has to be documented. In the Golimumab-monotherapy arm, rescue medication with simple analgesics or opioids for pain and stiffness control should be preferred, in case of insufficient efficacy NSAIDs in a dose of  $\leq 50\%$  of the maximal recommended dose could be used for a short-time period, but under no circumstance Celecoxib should be taken in the control group.

### 6.3 Study Population

A total of 170 patients with active AS fulfilling the modified New York criteria who have had an inadequate response to  $\geq 2$  NSAIDs will be enrolled in the study. It is expected that 100 patients will achieve a good clinical response to Golimumab at Week 12 and will be randomized to the core study phase.

#### 6.3.1 Inclusion Criteria

##### Phase I of the study:

1. Age  $\geq 18$  years.
2. Definite diagnosis of AS according to the modified New York criteria.
3. History of an inadequate response to adequate therapeutic trials with NSAID's, defined as at least two NSAID's over a 4-week period in total at maximum recommended or tolerated anti-inflammatory dose
4. Active disease as defined by a BASDAI value of  $\geq 4.0$  at screening and baseline.
5. Presence of at least one of the following risk factors for radiographic spinal progression:
  - Elevated CRP ( $>5\text{mg/l}$ ) at screening and the absence of reasons for elevated CRP other than AS;
  - Presence of  $\geq 1$  syndesmophyte on prior X-rays of the spine.
6. Subject is a candidate for anti-TNF therapy based on the investigator's opinion.
7. Subject is able and willing to give a written informed consent and comply with the requirements of the study protocol. Only patients who give written informed consent will be included in the trial.
8. If female: either unable to bear children (postmenopausal for at least 1 year or surgically sterile) or is willing and able to practice a reliable method of contraception throughout the study and 6 months after the last dose of study drug. A highly effective method of birth control is defined as those which result in a low failure rate (i.e. less than 1% per year) when used consistently and correctly such as implants, injectables, combined oral contraceptives or a vasectomised partner (at least 1 year prior to enrolment). In questionable cases of menopausal status a blood sample with simultaneous levels of

follicle stimulating hormone (FSH) above 40 U/l and estradiol below 30 pg/ml is confirmatory. The results of the pregnancy test performed at Screening must be negative.

9. If on NSAIDs: the dose must be stable for at least 2 weeks prior to baseline.
10. If on analgesics: the dose must be stable for at least 2 weeks prior to baseline.

Phase II of the study:

Achievement of an improvement of  $\geq 2$  absolute points (on a 0-10 scale) of the BASDAI after 12 weeks of Golimumab treatment in Phase I

